### Secondary Estimands

4.2

Secondary outcomes are defined per ICU care episode. ICU length of stay is the time from ICU admission to ICU discharge or death. The durations of invasive mechanical ventilation, noninvasive ventilation, and CRRT are the cumulative hours of each therapy during the ICU episode, as registered in SIR; because death precludes further accrual of these durations, they are analyzed in a time‐to‐event framework with death handled as a competing event. Unplanned ICU readmission is defined, per the SIR definition, as an unplanned return to intensive care within 72 h of ICU discharge, recorded as a binary outcome per discharged episode.

Testing‐intensity outcomes, referred to elsewhere in this protocol as process outcomes, are the number of ABG samples, venous laboratory tests, and chest radiographs per patient‐day.

The environmental outcome—climate impact expressed as carbon dioxide equivalents (CO_2_e, 100‐year global warming potential) attributable to blood gas sampling, laboratory testing, and chest radiography—will be estimated from the process‐outcome counts combined with published and supplier‐derived emission factors per test, with the functional unit being CO_2_e per patient‐day; a separate prespecified analysis plan will detail data sources, system boundaries, and methods, and this outcome is exploratory. Because death precludes the further accrual of tests and of their associated emissions, an intervention that increased early mortality would mechanically appear favorable on both testing intensity and CO_2_e. These outcomes are therefore subordinate to the primary safety outcome: they are interpreted as evidence of benefit only if non‐inferiority for 30‐day mortality is demonstrated, and if it is not, they are reported descriptively with no efficiency or environmental claim made. All such outcomes are expressed per patient‐day as well as per care episode, so that any shortening of the denominator through earlier death remains visible.

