ICU length of stay and the durations of invasive ventilation, noninvasive ventilation, and CRRT are analyzed in a time‐to‐event framework, with time origin at ICU admission (for length of stay) or at initiation of the respective therapy (for therapy durations). The events of interest are, respectively, live ICU discharge and liberation from the therapy; death before the event is treated as a competing event using cause‐specific Cox proportional‐hazards models with a gamma‐distributed cluster‐level frailty to account for clustering, complemented by cause‐specific cumulative incidence functions. Episodes are administratively censored at 30 days from ICU admission for length of stay, and from initiation of the respective therapy for the durations of invasive ventilation, noninvasive ventilation, and CRRT; episodes still ongoing at that point are censored. Treating death as a competing event rather than censoring avoids the bias whereby early deaths masquerade as short, favorable stays. Proportional‐hazards assumptions are assessed with Schoenfeld residuals; where violated, effects are reported as time‐varying or summarized as restricted‐mean‐survival‐time differences. Models are adjusted for the same covariates as the primary analysis. Unplanned ICU readmission within 72 h is analyzed among live ICU discharges with a logistic generalized linear mixed‐effects model specified analogously to the primary analysis.

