### Harms

5.9

The conceivable harms of reducing routine diagnostics are delayed recognition of clinical deterioration, of laboratory derangements such as electrolyte disturbance or occult bleeding, or of mechanical complications such as pneumothorax or catheter malposition that routine imaging might otherwise detect. Because the trial is embedded in routine care and modifies testing defaults rather than introducing a therapeutic agent, harms are monitored at two levels. At the population level, the monthly safety reports track 30‐day mortality and the secondary safety outcomes by cluster and intervention status; these outcomes are deliberately chosen as sensitive upstream indicators that would deteriorate before mortality.

At the patient level, clinicians and local investigators are instructed to report any serious adverse event suspected to be related to reduced testing, in particular missed or delayed diagnoses with clinical consequences, to the principal investigator without undue delay after becoming aware of it. Causality is assessed by the independent safety review group, which reviews the case documentation and classifies events as unrelated, possibly related, or probably related to the intervention. Confirmed or suspected intervention‐related serious harms and any safety signal in the monthly reports trigger review by the safety review group, which may recommend pausing the intervention at the affected ICU or across the trial; such events are reported to the steering committee, the affected ICU, and, where required under Swedish regulations, the Swedish Ethical Review Authority. All reported events and actions taken are summarized in the trial publication. Patients are covered by the ordinary Swedish patient‐injury insurance (patientförsäkringen, LÖF).

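### Escalation from noninvasive to invasive ventilation has no event status of its own and falls by default into 'liberation', which biases a supportive safety outcome toward apparent safety

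*Protocol article*

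**What the plan says.** Section 4.2 (Secondary Estimands) defines the outcome: "The durations of invasive mechanical ventilation, noninvasive ventilation, and CRRT are the cumulative hours of each therapy during the ICU episode, as registered in SIR". The two ventilation modes are counted separately. Death is the only event that section names as stopping further accrual.

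Section 5.2 sets the analysis. The clock starts "at initiation of the respective therapy (for therapy durations"). On the event and the competing event: "The events of interest are, respectively, live ICU discharge and liberation from the therapy; death before the event is treated as a competing event". The models are cause-specific Cox models with a cluster frailty. On censoring, at 30 days from the start of the therapy: "episodes still ongoing at that point are censored". The section justifies treating death as competing on the ground that early deaths would otherwise look like short, good stays.

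Neither section defines liberation or mentions a change from noninvasive to invasive ventilation. No listed outcome counts intubations.

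On the role of these outcomes, section 4.4 lists time on NIV among the patient safety metrics. Section 4.4.1 gives the more sensitive safety outcomes as the second ground for the 3-percentage-point margin. Section 5.8 puts the secondary safety outcomes into the monthly reports. Section 5.9 says of them: "these outcomes are deliberately chosen as sensitive upstream indicators that would deteriorate before mortality". Section 5.1 makes all secondary outcomes supportive, with no formal non-inferiority test.

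**The concern.** A course of NIV can end in recovery, in escalation to invasive ventilation, or in death. The plan separates the third from the first but gives the second no place. Take three records in which NIV is not resumed:

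- A: 48 h of NIV, then recovery. Event at 48 h.
- B: 6 h of NIV, then intubation. Not dead and not on NIV, so the only listed state left is the event, at 6 h.
- C: 6 h of NIV, then death. Competing event.

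If B is coded by default, it looks better than A. The plan's reason for separating early deaths applies equally to early NIV failures.

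The invasive-ventilation analysis does not recover the signal directly. Its clock starts when invasive ventilation starts, so it describes how long intubated patients stay ventilated and not how many are intubated. Section 5.9 names delayed recognition of deterioration as a conceivable harm, and a change in intubation after NIV is one place where that could appear. At stake is whether one of the outcomes meant to give early warning can move in the reassuring direction when patients do worse.

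**Working it through.** The documents state no figure for this outcome, so there is none to reproduce. All rates below are assumptions. The check concerns direction and size if escalation is pooled with liberation.

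**Formula.** With constant cause-specific hazards, let f be the share of control NIV courses ending alive that end in intubation, rw the hazard ratio (HR, intervention over control) for true weaning, and ri the HR for intubation. Then:

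- pooled HR = rw(1 − f) + ri·f
- HR with intubation as its own competing event = rw
- bias = f(ri − rw), which is positive whenever ri exceeds rw.

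**Recovery unchanged (rw = 1).** Assume a total control exit hazard of 0.5 per day, 5% of exits by death and 20% by intubation. The control hazards per day are 0.375 recovery, 0.10 intubation and 0.025 death. Raise intubation 1.5-fold, to 0.15:

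- pooled HR = (0.375 + 0.15)/(0.375 + 0.10) = 0.525/0.475 = 1.105; true HR 1.00
- share intubated: 20% to 0.15/0.55 = 27%
- share recovering: 75% to 0.375/0.55 = 68%
- mean NIV time: 1/0.5 = 2.0 days to 1/0.55 = 1.8 days.

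For a control failure share p of all exits, pooled HR = 1 + p(ri − 1)/0.95. At the ends of the grid:

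- p = 0.10, ri = 1.25: 1 + 0.025/0.95 = 1.03
- p = 0.30, ri = 2.0: 1 + 0.30/0.95 = 1.32.

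**Weaning also worse (rw = 0.9, true HR 0.90).**

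| f | pooled HR, ri = 1.3 | pooled HR, ri = 1.5 |
|---|---|---|
| 0.10 | 0.94 | 0.96 |
| 0.20 | 0.98 | 1.02 |
| 0.30 | 1.02 | 1.08 |
| 0.40 | 1.06 | 1.14 |

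The sign reverses when f > (1 − rw)/(ri − rw): above 0.1/0.4 = 0.25 for ri = 1.3, and above 0.1/0.6 = 0.17 for ri = 1.5. Below that, harm is attenuated but still visible.

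**One case on the absolute scale** (f = 0.30, rw = 0.9, ri = 1.5). Hazards per day for weaning, intubation and death are 0.35, 0.15 and 0.02 in control, and 0.315, 0.225 and 0.02 under intervention. A simulation of 400,000 courses per condition gave:

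- mean NIV time: 46.0 h to 42.9 h
- 'liberated' by 72 h, intubation included: 76.0% to 78.4%
- weaned without intubation by 72 h: 53.2% to 45.8%
- intubated: 28.8% to 40.1%.

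The first two lines look like improvement; the last two show the deterioration.

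**Opposite direction.** If delayed recognition postpones intubation, ri falls below 1. With f = 0.20, rw = 1 and ri = 0.8, the pooled HR is 0.80 + 0.16 = 0.96, which reads as unfavourable.

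**The case against.** A reader might infer that the plan scores intubation as success. The documents do not say so. Liberation is undefined and can be read as successful weaning, and section 2.5 says fuller versions of the protocol and analysis plan are deposited elsewhere. That objection stands against the strong reading. It does not close the gap. If liberation means weaning, the intubated patient has no listed state, and an analyst could code the episode as event, censored or competing, with different results. Section 2.5 also presents the article as both protocol and analysis plan, and section 5.2 is specific about origin, event, competing event and censoring.

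A reader might also infer that the outcome always points the wrong way under harm. It does not. The direction depends on how intubation and weaning change: the table shows plain attenuation at low intubation shares, and later intubation would read as unfavourable. Record B also depends on NIV not being resumed, because section 4.2 counts cumulative hours and NIV after extubation adds to them.

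The consequence is limited. Section 5.1 makes the outcome supportive, and both quantitative triggers in section 5.8 are based on mortality. Nor does section 5.8 say that the monthly reports use the Cox model. ICU length of stay, timed to live discharge with death competing, does not depend on how intubation is coded, and it could register worsening, as could 30-day mortality. Against this, section 5.8 also has units contacted after adverse changes in any secondary safety outcome, so the direction of each one matters.

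**Conclusion.** The point holds as a gap in the event definition, not as a stated scoring rule. With death the only competing event and day 30 the only censoring point, escalation from NIV to invasive ventilation defaults into the event of interest or is left without a state. If coded as the event, the outcome is biased toward apparent safety whenever the intubation HR exceeds the weaning HR.

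The size rests wholly on assumed rates: a pooled HR of about 1.03–1.32 against a true 1.00 for 10–30% control failure, 5% deaths, a 1.25- to 2.0-fold intubation hazard and unchanged recovery. With a true weaning HR of 0.90, the pooled value runs from 0.94 to 1.14 over the table. These figures illustrate the mechanism and do not predict this trial's result. The primary mortality analysis and its margin test are unaffected. The correction is worth making because the outcome is offered as an early safety indicator.

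**What to change.** In section 5.2:

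- Define NIV liberation as the end of NIV without subsequent invasive ventilation in the same ICU episode.
- Treat escalation to invasive ventilation as a competing event alongside death.
- Report the cause-specific HR and cumulative incidence of escalation next to the liberation result.
- State how NIV after extubation is handled, for example by reporting it separately, and align this with the cumulative-hours definition in section 4.2.

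The cost is wording, one extra cause-specific model and fewer liberation events. Under the assumptions above, events fall from 95% of control courses to 85–65%.

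The order of NIV and invasive ventilation within the episode must be available from the registry. Section 5.11.1.4 lists ventilation durations and does not show that start and stop times are extracted, so this should be confirmed first. Section 6.2 treats changes to the analysis plan as substantive amendments that need ethics approval. Section 2.5 states that no outcome data had been extracted or examined when the versions were finalized; if that is still so, the change can be credibly prespecified.

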### General Principles

5.1

Analysis of the primary outcome follows the intention‐to‐treat principle, with every care episode analyzed according to the randomized state of its cluster at the time of admission and irrespective of local adherence; a prespecified per‐protocol analysis is reported alongside it.Mixed‐effects models will account for clustering and temporal trends.Multiple imputation will address missing data when > 10% are missing for key covariates.Sensitivity analyses will explore the robustness of findings.Statistical significance will be set at *α* = 0.05 for superiority analyses and *α* = 0.025 (one‐sided) for non‐inferiority analyses.

No adjustment for multiplicity is made. Only the primary outcome supports a confirmatory conclusion; secondary, process, and exploratory outcomes are reported as point estimates with 95% confidence intervals (CIs) and interpreted as supportive, with no formal non‐inferiority testing applied to them.

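### For the ventilation and CRRT durations, liberation is undefined and only a prior death competes, so a therapy stopped at withdrawal of life support shortly before death can count as the favourable event

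*Protocol article*

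**What the plan says.** Section 5.2 defines the time-to-event outcomes together: "The events of interest are, respectively, live ICU discharge and liberation from the therapy; death before the event is treated as a competing event". For length of stay the event is live ICU discharge. For invasive ventilation, noninvasive ventilation and CRRT it is liberation, a term that the article does not define further. The only censoring described is administrative, at 30 days: "episodes still ongoing at that point are censored". The section then gives this assurance: "Treating death as a competing event rather than censoring avoids the bias whereby early deaths masquerade as short, favorable stays".

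Section 4.2 says that the therapy durations "are the cumulative hours of each therapy during the ICU episode, as registered in SIR", and justifies the competing-event approach "because death precludes further accrual of these durations". The reason for stopping is not part of the definition.

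Sections 5.11.1.4 and 5.11.1.5 list care limitations, withdrawal decisions and precisely timed mortality among the data extracted from the registry. No outcome definition or analysis rule in the article uses the withdrawal data.

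On the role of these outcomes, Section 5.1 states: "Only the primary outcome supports a confirmatory conclusion". Section 5.9 nevertheless describes the secondary safety outcomes as "sensitive upstream indicators that would deteriorate before mortality", Section 5.8 puts them in the monthly safety reports, and Section 4.4.1 cites them in support of the 3-point margin.

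**The concern.** When life support is withdrawn, the ventilator or CRRT can be stopped while the patient is still alive, with death following soon after. In that order of events the death does not precede the stop. If a stop is read as liberation, this patient is scored like one who was weaned and survived.

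This is separate from how a cause-specific Cox model handles competing deaths. Here the death is not recognised as competing at all and adds to the count of the favourable event.

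The direction matters. The three outcomes are meant to show deterioration early. If the intervention led to more deaths after withdrawal, this coding would push the liberation hazard ratio upwards, towards apparent benefit. Section 4.2 already protects the testing-intensity and CO2e outcomes against looking favourable because patients die sooner. The therapy durations have no equally complete protection.

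**Working it through.** **Step 1: apply the written rule.** Take three patients, each ventilated for five days.

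- Patient 1 is extubated and survives: liberation at day 5.
- Patient 2 dies on the ventilator: competing event at day 5.
- Patient 3 is extubated after a withdrawal decision and dies two hours later. The registered hours end with the patient alive, so death did not precede the stop. Therapy is not ongoing at 30 days, so the episode is not censored. If stop means liberation, the only remaining code is liberation at day 5.

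For length of stay, patient 3 dies in the ICU without live discharge and is correctly a competing event. The gap is confined to the three therapy durations.

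**Step 2: illustrate the size.** The plan states no figure for this, so there is none to reproduce. The inputs are:

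- Deaths among treated episodes: 18% in control. This is the all-episode 30-day mortality in Section 4.4.2, used as a stand-in because the article gives none for ventilated or CRRT patients.
- Deaths under intervention: 21%, that is 18% plus the 3-point margin.
- Share q of deaths in which therapy stops first: assumed 25%, 50% or 75%.
- Constant hazards, with liberation hazard L and death hazard D (deaths on therapy and deaths after withdrawal together).

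In control, D0/(L + D0) = 0.18, so on a relative scale L = 82 and D0 = 18. Under intervention with L unchanged, D1 = 82 × 0.21/0.79 = 21.80. The correct liberation hazard ratio is 1.00. The scored one is (L + q·D1)/(L + q·D0):

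- q = 0.25: (82 + 5.45)/(82 + 4.5) = 87.45/86.5 = 1.011
- q = 0.50: (82 + 10.90)/(82 + 9) = 92.90/91 = 1.021
- q = 0.75: (82 + 16.35)/(82 + 13.5) = 98.35/95.5 = 1.030

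The share of control liberations that are really withdrawal deaths is q·D0/(L + q·D0): 4.5/86.5 = 5.2%, 9/91 = 9.9% and 13.5/95.5 = 14.1%.

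**Step 3: vary the assumptions.**

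- Total hazard held fixed, so that more deaths mean fewer liberations. The correct hazard ratio is 79/82 = 0.963. The scored values are (79 + 5.25)/86.5 = 0.974, (79 + 10.5)/91 = 0.984 and (79 + 15.75)/95.5 = 0.992. A harmful ratio moves towards 1 but stays below it.
- Mortality of 24% under intervention, twice the margin. D1 = 82 × 0.24/0.76 = 25.89, and the scored hazard ratios are 1.023, 1.043 and 1.062.
- Mortality of 35% among treated control patients (an assumption). The share of scored liberations that are withdrawal deaths is 0.35q/(0.65 + 0.35q): 11.9%, 21.2% and 28.8%.

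In every scenario the any-stop coding shifts the hazard ratio in the favourable direction when mortality is higher under intervention.

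**The case against.** Three objections deserve weight.

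**The reading.** A reader might infer that the plan scores withdrawal of life support as liberation. No section says so. In the clinical sense of successful weaning, a patient taken off support to die is never liberated, and the later death is then a death before the event, which competes under the existing text. This stands: the defect is that two opposite codings of the same patient are both open. The weaning reading, however, has no survival or reason-for-stop criterion behind it, and it places the event time beyond the registered hours that Section 4.2 uses.

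**Condensation.** Section 2.5 says that fuller versions of the protocol and analysis plan are deposited with the registration record, and these may define liberation. The same section calls this publication both protocol and analysis plan, and Section 5.2 goes beyond a summary by fixing event, competing event, time origin and censoring. A rule stated in that detail should be unambiguous.

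**The assurance and the size.** A reader might also infer that the plan's sentence about early deaths is wrong. It speaks of stays and is right for length of stay. The size rests on an assumed share of deaths after a stop. In addition, 18% covers all episodes and includes deaths after genuine liberation, so it is not the correctly coded incidence of competing death. The shift is small at the margin. Total mortality remains visible in the primary analysis and in the monthly reports, whatever the order of stop and death. All of this stands and limits the point. It does not remove it, because these outcomes are meant to give warning before mortality does.

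**Conclusion.** The point holds for invasive ventilation, noninvasive ventilation and CRRT. Section 5.2 leaves liberation undefined and lets only a prior death compete, while Section 4.2 measures registered hours. Coded that way, a stop at withdrawal followed shortly by death enters the favourable event.

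The illustrative distortion is modest: a hazard ratio of about 1.01 to 1.03 where the truth is 1.00, with 5–14% of control liberations being withdrawal deaths. This rests on constant hazards, 18% versus 21% mortality among treated episodes, and an assumed 25–75% of deaths after a stop.

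The outcomes are supportive and the primary 30-day mortality analysis is untouched. The coding should still be settled before analysis, because the plan relies on these outcomes as safety indicators and the error runs in the direction that hides harm.

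**What to change.** This concerns analysis coding only and says nothing about when therapy should be stopped. In Section 5.2:

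1. Define liberation, for the three therapy durations, as end of therapy with the patient alive for a prespecified short interval afterwards (for example 24 h).
2. Classify a stop followed by death within that interval as the competing event, dated at the stop.
3. Use the registry's withdrawal field as well, where its content and timing allow. The article does not show that withdrawal decisions are recorded by therapy or time-stamped, so this should be checked first.
4. Report the number of such stops by condition.
5. Keep the any-stop coding as a sensitivity analysis.

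The cost is a few lines of text and a recode. Precise death times are already in the extract. Dated therapy stops are also needed and should be confirmed, since the article lists durations only. The interval is arbitrary, and the any-stop analysis shows how much the result depends on it. Section 2.5 states that no outcome data had been examined when the versions were finalized. If that is still so, the rule can be prespecified.

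### The length-of-stay and therapy-duration hazard ratios censor deaths, although Section 5.2 says otherwise, and no adjusted contrast that keeps deaths in the risk set is stated

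*Protocol article*

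**What the plan says.** The last paragraph of Section 5.2 analyses ICU length of stay and the durations of invasive ventilation, noninvasive ventilation and CRRT as times to event. "The events of interest are, respectively, live ICU discharge and liberation from the therapy". As to deaths, "death before the event is treated as a competing event using cause‐specific Cox proportional‐hazards models", with a gamma frailty for cluster, "complemented by cause‐specific cumulative incidence functions". On the horizon: "Episodes are administratively censored at 30 days from ICU admission for length of stay"; therapy durations have the same limit counted from the start of therapy. Where hazards are not proportional, time-varying effects or restricted-mean differences are the fallback. The paragraph then justifies the approach: "Treating death as a competing event rather than censoring avoids the bias whereby early deaths masquerade as short, favorable stays". On adjustment it says: "Models are adjusted for the same covariates as the primary analysis".

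Section 4.2 (Secondary Estimands) says that the therapy durations "are the cumulative hours of each therapy during the ICU episode".

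Section 4.4.1 gives the secondary safety outcomes as the second ground for the 3-point margin, expecting them to worsen before a mortality effect could be seen. Section 5.9 (Harms) repeats that expectation.

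**The concern.** Section 5.2 sets competing-event handling against censoring as if they were alternatives. For the regression it names they are the same thing. A cause-specific model for live discharge drops a patient from the risk set at death, exactly as if that patient had been censored. Its hazard ratio compares discharge rates among patients still alive and in the ICU, and says nothing about how many died.

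This matters because four of the five registry secondary outcomes use this model, and Sections 4.4.1 and 5.9 treat those outcomes as early warnings. A hazard ratio near 1 for discharge or liberation could be presented as evidence of safety although it is, by construction, blind to a pure rise in deaths. The component that is not blind, the cumulative incidence function, has no stated adjusted comparison between conditions.

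**Working it through.** **Is there a figure to reproduce?** No. The protocol gives no expected effect or power for these models, so the check is of the method.

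**Step 1: the likelihood.** Let T be the time of exit from the ICU by any route. Each live discharge at time t contributes the factor exp(βx_i + …) / Σ exp(βx_j + …), summed over episodes j with T_j ≥ t. A death contributes no factor and leaves every later sum. Coding the death as censored at T gives the same expression. The cluster frailty does not change this.

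**Step 2: inputs.** From the protocol: 30-day horizon, 3-point margin, 22,428 episodes, baseline 30-day mortality 18%. Assumed, because the protocol does not give them: constant hazards; a live-discharge hazard λ_d = 0.30 per day in both conditions; control ICU mortality of 8%, 12% or 18%; and 3 points more ICU deaths under the intervention.

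**Step 3: formulas.** With death hazard λ_m, the cumulative incidence of cause k by day 30 is

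CIF_k = λ_k / (λ_d + λ_m) × [1 − exp(−30(λ_d + λ_m))].

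The bracket is practically 1. For 18% to 21% deaths:
- λ_m = 0.30 × 0.18/0.82 = 0.0659, rising to 0.30 × 0.21/0.79 = 0.0797.
- Cause-specific HR for death = 0.0797/0.0659 = 1.21.
- Cause-specific HR for discharge = 0.30/0.30 = 1.00.
- Live discharge by day 30 = 0.30/0.3659 = 82.0%, falling to 0.30/0.3797 = 79.0%.
- Approximate subdistribution HR = ln(1 − 0.79)/ln(1 − 0.82) = 0.91.

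| ICU deaths | HR discharge (planned) | HR death | Live discharge by day 30 | Approx. subdistribution HR |
|---|---|---|---|---|
| 8% → 11% | 1.00 | 1.42 | 92.0% → 89.0% | 0.874 |
| 12% → 15% | 1.00 | 1.29 | 88.0% → 85.0% | 0.895 |
| 18% → 21% | 1.00 | 1.21 | 82.0% → 79.0% | 0.910 |

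**Step 4: simulation.** 200 trials of 22,428 episodes were simulated for the last row, with individual allocation and no clustering. The mean discharge HR was 1.000, with p < 0.05 in 3% of trials, no more than chance. The death HR averaged 1.21. Live discharge fell by 3.0 points on average (SD across trials 0.54 points; clustering and period adjustment would widen this).

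**Step 5: the fallback.** A restricted mean to day 30 with deaths censored is (1 − e^(−0.30 × 30))/0.30 = 3.33 days in both conditions, so it is equally blind.

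**Step 6: unequal frailty.** Suppose 30% of patients leave slowly (0.10 against 0.40 per day), the extra deaths fall on them (death hazard 0.06 to 0.085 per day, against 0.02 in the rest), and this is not adjusted for. Deaths rise from 14.5% to 17.0%. The discharge HR is 1.03 (95% CI 1.00 to 1.05, 20,000 episodes per condition), slightly favourable, while live discharge falls from 85.3% to 82.8%.

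**Step 7: definitions side by side.** Section 4.2 counts total hours on the therapy in the episode. Section 5.2 measures from the first start to liberation. The two differ whenever a therapy is stopped and restarted. An episode without the therapy has zero cumulative hours under Section 4.2 but has no time origin under Section 5.2.

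**The case against.** Several points on the other side are sound.

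- **Cumulative incidence functions are planned.** They treat death as competing and would show the fall from 82% to 79%. A reader might infer that these outcomes as a whole can show no signal while deaths rise. That is true of the hazard ratio and of a death-censored restricted mean, not of the whole planned analysis.
- **The named bias is largely avoided.** A reader might infer that early deaths will be scored as short, good stays. They will not, because only live discharge or liberation counts as the event. The reason given is wrong; the consequence claimed is mostly right.
- **Deaths are measured directly.** Thirty-day mortality is the primary outcome, Section 5.8 has it reviewed monthly with a trigger at a pooled difference above 3 points, and Section 5.1 makes the secondary outcomes supportive only. The documents do not support a reading that excess mortality would go undetected.
- **The hazard ratio suits one kind of harm.** If reduced testing slowed recovery among survivors, the discharge hazard would fall and the ratio would show it.
- **Calendar time.** Section 5.2 lists period effects apart from the baseline covariates and carries over only the covariates, so a reader might infer that month is left out. Section 5.1 says that mixed models account for temporal trends, and the Discussion says that calendar time is modelled. This is an ambiguity, not a shown omission.
- **Selection into therapy.** That fewer blood gases change who starts ventilation or CRRT is conjecture; Section 3.6 leaves clinically indicated testing unrestricted.

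The deposited full plan may also hold more detail. None of this rescues the contrast with censoring, which misdescribes the named model, or supplies an adjusted effect measure here that keeps deaths in the risk set.

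**Conclusion.** The point holds in a limited form. Section 5.2 misdescribes its own regression: the cause-specific hazard ratio censors deaths and stays at 1.00 under any rise in deaths that leaves the discharge hazard unchanged, including a rise of the full 3 points. That result needs no assumed rates. The accompanying fall of 3.0 points in live discharge holds at all three ICU mortalities tried, but rests on constant hazards and on the extra deaths occurring in the ICU within 30 days. The slightly favourable ratio of 1.03 depends on one assumed pattern of frailty and is only an illustration.

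The only adjusted effect measure named in the main analysis of these outcomes is therefore the one that cannot see excess death. Crude cumulative incidence curves cannot stand in for it, because later months hold more intervention time. The effect is on how much reassurance these outcomes add to the margin argument in Section 4.4.1 and the harms plan in Section 5.9. The primary analysis and the detection of mortality are untouched. The mismatch between cumulative hours and time to liberation is a separate, smaller inconsistency that needs settling.

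**What to change.** 1. Remove the contrast with censoring from Section 5.2. Say that deaths are not counted as discharges or liberations, and that the hazard ratio is conditional on being alive and still in the ICU or on the therapy.
2. Report the cause-specific hazard ratio for death beside the one for discharge or liberation, for each of the four outcomes.
3. Report an adjusted day-30 difference in the cumulative incidence of live discharge or liberation, or a subdistribution hazard ratio, with 95% CI and with clustering and calendar period accounted for.
4. State that categorical calendar month is in these models.
5. Reconcile Sections 4.2 and 5.2 on therapy duration: choose cumulative hours or time to liberation, and say how restarts and episodes without the therapy are handled.

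The data are already in the registry, so the cost is modest programming and more estimates to report. Section 6.2 classes changes to the analysis plan as substantive, so an amendment would be needed. Section 2.5 says that no outcome data had been extracted or examined when the protocol versions were finalized; the change should likewise precede extraction.
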